### Exposures

In FIRST-ABC step-up, children randomised to HFNC were started at a flow rate based on body weight. When a child was deemed ready for weaning, the flow rate was reduced by 50%. Children randomised to CPAP were started at a pressure of 7–8 cm H_2_O. When a child was deemed ready for weaning, the pressure was reduced to 5 cm H_2_O. Both HFNC and CPAP were delivered through devices and interfaces already used as part of routine care at sites. For both groups, the fraction of inspired oxygen (FiO_2_) was titrated to maintain peripheral oxygen saturation (SpO_2_) of 92% or higher. Clinicians were permitted to switch from HFNC to CPAP (or vice versa) or escalate to other modes of NRS or invasive mechanical ventilation if prespecified treatment failure criteria were met (FiO_2_ ≥0.60, severe respiratory distress, patient discomfort).

In this study, exposure groups will include children who started HFNC or NIV, as per daily interventions in the PICANet Admission Data Collection Form.^12^ CPAP is not recorded in the PICANet daily procedures and, therefore, it cannot be identified. As NIV cannot be used to record HFNC, we will use NIV as a surrogate for CPAP, providing treatment strategies for the TTE.^18^

The assumption that NIV could approximate CPAP was tested on the FIRST-ABC step-up population linked to the relevant PICANet sample using a previously reported strategy.^19^ Of the children with a recorded activity date that matched the randomisation date, or the following date, 86% of children with recorded NIV were assigned to CPAP in FIRST-ABC step-up and 86% of children with recorded HFNC were assigned to the same treatment in FIRST-ABC step-up.

### Covariates

We will use demographic and admission information to create a cohort of children that reflects the FIRST-ABC step-up sample.

Potential covariates collected at PICU admission that will be explored using directed acyclic graphs (DAGs) include, but are not limited to: age, site, ethnic group, sex, type of admission to unit, previous PICU admission, source of admission, care area admitted from, elective admission, main reason for admission, cardiac arrest before PICU admission, cardiomyopathy or myocarditis, severe combined immune deficiency, hypoplastic left heart syndrome, leukaemia or lymphoma, liver failure, acute necrotising enterocolitis, spontaneous cerebral haemorrhage, neurodegenerative disorder, HIV, bone marrow transplant receiver, systolic blood pressure, SpO_2_, FiO_2_, arterial PaO_2_, base excess, lactate, mechanical ventilation, CPAP, pupil reaction.^20^

In addition, other daily interventions as defined by the PICANet Manual will be assessed as potential covariates from PICU admission up to the start of treatment.^18^

### Outcomes

The following outcomes will be measured:

Primary endpoint:

Time to liberation from respiratory support, defined as the start of a 2-day period free of all forms of respiratory support. Children discharged from PICU will be assumed to be liberated from all forms of support.

Secondary endpoints:

Mortality at PICU discharge.Rate of intubation at day 2.Duration of PICU stay.

### Subgroups

Subgroup analyses will be performed to test for interactions between the effect of starting treatment and the following baseline covariates, as pre-specified in the FIRST-ABC protocol:

Age (<12 months vs ≥12 months).SpO_2_:FiO_2_ ratio at baseline (within five categories at quintiles of the continuous variable).Reason for admission (bronchiolitis vs other respiratory vs cardiac vs other reason).

### Sample size considerations

In the design of the FIRST-ABC step-up RCT, it was anticipated that 508 observed events would achieve 90% power with a one-sided type I error rate of 2.5% to exclude the prespecified non-inferiority margin of an HR of 0.75. To account for censoring from death or transfer and refusal or withdrawal of consent, the target sample size was set at 600 children.^5^

The design of the TTE recognises that between 2019 and 2022 there were 14 875 respiratory admissions in PICANet.^21^ From a previous PICANet sample of 2 years, it was anticipated that more than 3000 children (of which 2/3 assigned to HFNC) would meet the pre-defined eligibility criteria and start the study treatments in the first 2 days of critical care admission. The primary outcome will be tested for non-inferiority using the RCT margin (corresponding to approximately a 16-hour increase in median time to liberation), and the secondary outcomes for superiority. Among the secondary outcomes, the rate of intubation at 48 hours was considered of high importance by patient representatives. With a proportion of 15.4% from FIRST-ABC step-up results, we anticipate that, with unequal group sizes, a two-sided type I error rate of 5%, and 90% power, the study will be able to detect a 4% absolute difference in proportions.^22^

### Statistical analysis (1)—frequentist approach

#### Planned analyses

The FIRST-ABC step-up primary outcome analysis was based on a mITT population, excluding children with no recorded respiratory support post-randomisation.^16^ To emulate the target trial primary analysis, the study will take a mITT approach, where each child will contribute to the original treatment group they started, irrespective of which treatments they may initiate later. Children will be followed until the date of their last recorded respiratory support or date of death.

To describe child characteristics, means, SD, medians and 25th and 75th percentiles will be calculated for continuous variables. Counts and percentages will be reported for categorical variables. The balance of baseline characteristics between treatment arms will be assessed.^23^

For the primary endpoint, the Kaplan-Meier method will be used for a crude comparison of time to liberation from respiratory support. To reduce the risk of bias due to model misspecification, doubly robust (DR) methods will be implemented for the analysis of the primary and secondary outcomes.^24 25^ This process involves fitting two models, one for the treatment and one for the outcome. The double-robustness property ensures statistical consistency of the estimator provided that at least one of the models is correctly specified.^26^

The DR methods that will be explored include augmented inverse probability treatment weighting (AIPTW) and targeted maximum likelihood estimation (TMLE).^27 28^ AIPTW improves the IPTW estimator by making use of the prognostic information in the conditioning set of the outcome model.^29^ TMLE is a substitution estimator that incorporates an outcome model and a propensity score model through a targeting step and implements non-parametric machine learning algorithms, which are more flexible than restrictive parametric models.^30 31^

Candidate methods will be investigated in terms of performance and ease of implementation, and details of the planned analysis will be included in the statistical analysis plan.

Adherence to the exposure will be measured as the proportion of children who switched to the other exposure, by treatment group. The percentage of children experiencing one or more protocol deviations will be compared between treatment groups using a χ^2^ test.^32^

#### Sensitivity analyses

To assess the risk of immortal time bias, a sensitivity analysis will exclude children who were assigned to the treatment on the day after their PICU admission. This will further align the timing of eligibility assessment with treatment assignment.

Additional sensitivity analyses will compare the primary method with other suitable strategies, including DR and non-DR methods, like G-computation.^33 34^ Where required, the balance of baseline analysis covariates between treatment arms will be assessed before and after propensity score weighting.^23^

To test the no unmeasured confounding assumption, a placebo test, also known as negative control, will be implemented.^35^,^38^ Single cubicle occupancy in the first 2 days of admission will serve as the negative control outcome.

### Statistical analysis (2)—Bayesian approach

#### Planned analyses

The primary and secondary outcomes will be re-analysed using a Bayesian approach. This will provide a comparison with the frequentist approach, and we will discuss the advantages and drawbacks of the two strategies. Bayesian alternatives to the planned statistical analysis (1) methods will be explored by performance and ease of implementation.^39^,^41^

For key outcome measures, the posterior distribution will be presented and summarised.^42^ Sensitivity of the results to different priors will be explored.^43^

The results from the Bayesian analysis will additionally serve for future work as outlined in the Future work section.

### Missing data

The amount of missing data is expected to be minimal. The level, pattern and reasons for data missingness will be explored, and the plausibility of the missing at random assumption for missing data will be considered (using clinical knowledge and DAGs).^44^ If required, in the statistical (1) approach, missing baseline variables will be imputed using the multivariate imputation by chained equations algorithm, with at least five imputations.^45^ In the statistical (2) approach, an appropriate Bayesian multiple imputation strategy for handling missing data will be used if required.^46^

### Validation of results against FIRST-ABC step-up

Results will be compared with the FIRST-ABC step-up findings in the mITT population.

To quantify the difference in the effect size, the standardised difference between the RCT and the emulation results will be calculated.

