In these settings, RCTs may benefit from being supplemented with additional data. Routinely collected healthcare data provides an alternative information source, offering opportunities for complementing RCTs, including increased strength for more precise estimation of secondary endpoints and subgroup analysis. However, inherent biases (eg, confounding by indication) and the quality and detail of data are a drawback to their use in this context. The recent development of the target trial methodology aims to mitigate some of the biases common to routine data by applying the study design principles of RCTs to non-randomised studies.^10 11^

This protocol defines a strategy to emulate the FIRST-ABC step-up RCT using routinely collected data. This RCT was deemed feasible to emulate using routine data from a high-quality healthcare database, the Paediatric Intensive Care Audit Network (PICANet).^12^ A successful emulation will be defined by comparable estimates with the target trial.^13^

This target trial emulation (TTE) will expand the findings from the FIRST-ABC step-up RCT, offering additional insights from real-world data, and will provide a case study for future work on assessing comparative effectiveness when combining evidence from an RCT and a TTE.^14 15^

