### Aim

This study aims to emulate the FIRST-ABC step-up RCT using an observational study design, and benchmark the results against the published trial. We will use advanced quantitative methods to minimise the impact of confounding by indication and allow for heterogeneity according to child characteristics. The analysis will be repeated using a Bayesian approach for follow-up research.

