### FIRST-ABC step-up

FIRST-ABC was a master protocol of two pragmatic randomised trials to evaluate the non-inferiority of HFNC versus CPAP for NRS in paediatric critical care.^16^ For the present study, we will focus on the step-up RCT which includes critically ill children requiring NRS for an acute illness. This was powered for the primary endpoint: a sample size of 536 children was required to achieve 90% power with a one-sided type I error rate of 2.5% to exclude the prespecified non-inferiority margin of an adjusted HR of 0.75, and anticipating 5% censoring due to death or transfer. To allow for withdrawal/refusal of deferred consent, the total sample size included 600 children.^17^ Of the 600 children randomised between August 2019 and November 2021, 573 were included in the primary analysis to measure time to liberation from respiratory support using a frequentist approach. This used a modified intention-to-treat (mITT) population, which only included participants who initiated treatment. HFNC met the non-inferiority margin criterion (HR 1.03, 95% CI 0.86 to 1.22). Similar results were seen in the per-protocol analysis (HR 1.03, 95% CI 0.86 to 1.23). Secondary outcomes included mortality at critical care unit discharge (OR 1.22, 95% CI 0.32 to 4.62) and intubation at 48 hours (OR 0.99, 95% CI 0.61 to 1.62). A summary of the components of the FIRST-ABC step-up emulation is reported in table 1.

**Table 1 T1:** Specification of the FIRST-ABC step-up emulation

Protocol component	FIRST-ABC step-up RCT	Target trial emulation
Eligibility criteria	Critically ill children requiring NRS for an acute illness were eligible if meeting the following:	Children included in PICANet between 1 August 2018 and 31 March 2022 and starting HFNC or NIV (as a surrogate for CPAP) will be eligible if meeting the following:
	*Inclusion criteria*	*Inclusion criteria*
	1) Admitted/accepted for admission to PICU/HDU.	1) Admitted to PICU.
	2) Age >36 weeks corrected gestational age and <16 years.	2) Age >36 weeks corrected gestational age and <16 years.
	3) Assessed by the treating clinician to require non-invasive respiratory support for an acute illness.	NA
	*Exclusion criteria*	*Exclusion criteria*

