## Strengths and limitations

This TTE will benefit from the large available sample size provided by the PICANet database, as well as its representative coverage of the FIRST-ABC step-up target population.

FIRST-ABC step-up will be emulated within the constraints of routinely collected data. As in any observational study, confounding and selection bias are major concerns. We will mitigate these risks through the TTE design and a validated and rich covariate data set, which will enable the key trial eligibility criteria to be applied, and most potential confounders to be included in the adjustment.

The inclusion of healthier children compared with FIRST-ABC step-up could dilute the effect towards the null, while failing to exclude children who initiated treatment before PICU admission could artificially shorten the follow-up period, further biasing the effect towards the null. In both cases, the bias is assumed to be non-differential. Other non-replicable exclusion criteria are contraindications to the treatments, and their unavailability in PICANet is mitigated by the treatment initiator design.

Study treatments and endpoints replication is constrained by the limits imposed by routinely collected data, but preliminary checks have proved NIV to be a valid alternative to CPAP.

Because the primary outcome cannot be assessed beyond PICU discharge, we will assume that respiratory support ends at the time of PICU discharge. This assumption may introduce differential bias as HFNC is more likely than CPAP to be continued on the ward.^49^

The use of daily rather than hourly data may limit our ability to target a population fully comparable to that in FIRST-ABC and may hinder accurate identification of the treatment received. Strategies will be implemented to minimise potential differences between treatment groups.

Additionally, DR analysis methods will be implemented, and sensitivity analyses will be performed to assess the robustness of the findings. Missing data are expected to be minimal.

This study will be reported using the Strengthening the Reporting of Observational Studies in Epidemiology guidelines.^50^

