## Ethics approval

This is a secondary data analysis project, which will use de-identified data from the PICANet database and from the FIRST-ABC step-up trial. PICANet has support and approval from the Health Research Authority Confidentiality Advisory Group to process confidential patient information without consent for research purposes under Regulation 5 of the Health Service (Control of Patient Information) Regulations 2002 (‘section 251 support’ of the NHS Act 2006) for data collected in England and Wales. The reference is 21/CAG/0098 and support is reviewed annually. In addition, the research database has ethics approval granted by the East Midlands—Derby Research Ethics Committee (ref. 18/EM/0267) and annual reports are provided to the committee.^51^ PICANet applies the National Data Opt-Out to the PICANet research database to ensure that no children are included in any research projects where an opt-out has been applied.^52^ The FIRST-ABC master protocol of trials received a favourable ethics opinion from the NHS East of England—Cambridge South Research Ethics Committee (reference number: 19/EE/0185) and approval from the Health Research Authority (Integrated Research Application System (IRAS) number: 260536).^16^

The study protocol was reviewed and received ethics approval from the London School of Hygiene & Tropical Medicine (LSHTM) Research Ethics Committee (reference number: 31369).

The interpretation and conclusions contained in this protocol are those of the authors alone.

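### The benchmark against FIRST-ABC step-up compares effects averaged over two case mixes, so part of any difference or agreement may not come from the emulation method

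*Protocol article*

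**What the plan says.** The Background of the protocol article sets the criterion: "A successful emulation will be defined by comparable estimates with the target trial". The section on validation of results gives the comparison, "Results will be compared with the FIRST-ABC step-up findings in the mITT population", and the statistic: "the standardised difference between the RCT and the emulation results will be calculated". It names no common population for the two estimates.

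On the populations, Table 1 lists three inclusion and nine exclusion criteria for the trial. One inclusion and six exclusions have no counterpart in the emulation. The trial's first inclusion criterion reads "1) Admitted/accepted for admission to PICU/HDU", whereas the emulation takes PICU admissions only. Strengths and limitations expects healthier children than in the trial and concedes that daily data may prevent full comparability with the trial population.

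On effect modification, the Aim is to "allow for heterogeneity according to child characteristics". The Subgroups section plans interaction tests for age, SpO2:FiO2 ratio and reason for admission.

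The Covariates section states an intention to build a cohort resembling the trial sample, but gives no method for this beyond selecting children. According to Ethics approval this is a project "which will use de-identified data from the PICANet database and from the FIRST-ABC step-up trial".

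**The concern.** An average treatment effect belongs to the population over which it is averaged. If a baseline variable modifies the hazard ratio and has a different distribution in the two samples, two unbiased studies will report different average effects. A biased emulation may also match the trial because case mix happens to offset the bias. The raw standardised difference adds these components together.

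Strengths and limitations treats the healthier mix as a bias that dilutes the effect towards the null. If the effect does vary with severity, a healthier cohort has a different average effect, which is a change of estimand and not a fault of the emulation.

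The stake is interpretive. The comparison is meant to show how well routine data reproduce the trial, and Future work intends to combine trial and emulation evidence. Both uses need to know how much of the difference comes from the method and how much from the children included.

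**Working it through.** **The protocol's own figures.** It gives no expected value for the benchmark. Its trial result is usable: "HFNC met the non-inferiority margin criterion (HR 1.03, 95% CI 0.86 to 1.22").

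- SE of the trial log HR = ln(1.22/0.86)/(2 × 1.96) = 0.350/3.92 = 0.089.
- Check: the design in Sample size considerations (508 events, 1:1) implies 2/√508 = 0.089, which agrees. The 508 events reproduce: 4 × (1.960 + 1.282)²/(ln 0.75)² = 508.

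**Emulation precision.** Sample size considerations expects more than 3000 children, two thirds on HFNC. I assume 3000 children and events in 95%, that is 2850.

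- SE = 1/√(2850 × 2/3 × 1/3) = 1/√633.3 = 0.040.
- Trial participants are excluded from the emulation, so the samples can be treated as independent: SE of the difference = √(0.089² + 0.040²) = 0.098.

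**Criteria count.** Inclusions 1 of 3 plus exclusions 6 of 9 = 7 of 12 marked NA.

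**Case-mix contribution with no bias at all.** With two strata and log HRs averaged by stratum share (an approximation), the gap is the difference in stratum share × ln(ratio of stratum HRs). The documents give neither quantity, so the following inputs are assumptions: HR 0.85 or 0.90 in one stratum and 1.20 in the other, with the first stratum 50% or 60% of the trial and 30% of the emulation.

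| Share difference | Stratum HRs | Gap in log HR | Standardised units |
|---|---|---|---|
| 20 points | 0.90, 1.20 | 0.2 × 0.288 = 0.058 | 0.59 |
| 30 points | 0.90, 1.20 | 0.3 × 0.288 = 0.086 | 0.88 |
| 20 points | 0.85, 1.20 | 0.2 × 0.345 = 0.069 | 0.71 |
| 30 points | 0.85, 1.20 | 0.3 × 0.345 = 0.103 | 1.06 |

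**Wider range of assumptions.** A stratum HR ratio of 1.25 with a 10-point shift gives 0.23 units. A ratio of 1.5 with 20 points gives 0.83, and a ratio of 2.0 with 30 points gives 2.13. A ratio of 1.0 gives zero, whatever the shift.

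**Against the noise.** The protocol states no cut-off, so I use 1.96 as a yardstick. Agreement then covers HR ratios from exp(−1.96 × 0.0977) = 0.83 to exp(1.96 × 0.0977) = 1.21, that is, emulation HRs of about 0.85 to 1.25 around 1.03. If the emulation SE is 1.5 times larger, the range is 0.835 to 1.271. The four tabulated gaps correspond to HR ratios of 1.06 to 1.11 and lie inside the range. A pure bias of HR ratio 0.90 would exceed the yardstick only 19% of the time, and one of 0.85 38% of the time. Case-mix effects and biases of this size could therefore offset each other unnoticed.

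**The case against.** Several points on the other side have force.

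- The populations may be closer than the count of 7 in 12 suggests. Requiring that HFNC or NIV was started partly covers two of the missing criteria (judged to need support; another form chosen). Excluding planned admissions plausibly moves the cohort towards the trial's acute-illness criterion, so it should not be counted as a mismatch. Strengths and limitations argues that the remaining missing exclusions are contraindications, mitigated by the initiator design. This weakens the evidence of mismatch, but HDU care and the expected healthier mix remain.
- Allowing for heterogeneity is not the same as expecting it. This stands: without a modifier that also differs in distribution there is no case-mix gap.
- The planned subgroup estimates use the same three covariates and would permit an informal check. True, but the validation section does not commit to a comparison by stratum.
- The article condenses a fuller plan. The choice of doubly robust estimator is expressly left to the analysis plan, which is not shown. The benchmark statistic, however, is stated, and nothing about its population is deferred. The intention to mirror the trial sample does not alter that statistic.

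A reader might also infer that the claim of "representative coverage of the FIRST-ABC step-up target population" contradicts the listed differences. The documents do not support that. The phrase concerns the target population rather than the enrolled sample, PICANet records all PICU admissions in the UK and Ireland, and the limits are disclosed in the same section and in Table 1.

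**Conclusion.** The point holds in a conditional form. The stated benchmark sets side by side two averages over populations that the protocol expects to differ, while the protocol leaves room for effect modification. If a modifier is distributed differently in the two samples, neither a difference nor agreement can be attributed to the emulation method alone.

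The size is unknown. The 0.6 to 1.1 standardised units rest on assumed stratum HRs and shares, on 3000 children with 95% events, and on averaging log HRs. They are modest beside the trial's own SE of 0.089, and zero without effect modification.

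A reader might go further and infer that the benchmark cannot show whether the emulation succeeded. The documents do not support that: comparability of the estimates, as the protocol defines success, can still be assessed. What is weakened is the explanation of the result. This makes the change a worthwhile, inexpensive improvement and not the repair of an invalid analysis.

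**What to change.** Keep the PICANet-population estimate as the real-world result and keep the raw standardised difference. Beside it, report a second standardised difference, computed from an emulation estimate standardised to the FIRST-ABC step-up mITT distribution of covariates held in both sources, at least age, SpO2:FiO2 and reason for admission. Either average the doubly robust outcome model over the trial children or weight the emulation cohort by inverse odds of trial membership. Add a table of baseline characteristics, trial against emulation, so that the reader can see where the samples differ.

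The project states that it will use trial data, and the Exposures section reports that the trial population has already been linked to the relevant PICANet sample, so shared covariates should be obtainable.

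The cost is wording in the analysis plan, one extra analysis and a somewhat wider interval for the standardised estimate. It will not reduce the trial's own uncertainty. The criteria marked NA, the use of NIV for CPAP, and the assumption that support ends at PICU discharge cannot be aligned in this way and should remain stated as limitations of the comparison.
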